## Abstract

**Introduction:**

Aneurysmal subarachnoid haemorrhage (aSAH) is a severe condition associated with significant morbidity and case fatality rate. Delayed cerebral ischaemia (DCI) is a major factor contributing to poor outcomes. For long, DCI was thought to be caused by vasospasm, induced by blood in the subarachnoid space. Growing experimental and clinical evidence has shown an activation of the coagulation cascade and several other (intravascular) pathophysiological pathways, affecting the cerebral microcirculation. In a retrospective analysis of our aSAH patient registry, we observed lower in-hospital mortality and a significantly higher rate of discharge-to-home in patients treated with high-dose nadroparin, compared with patients treated with low-dose (prophylactic) nadroparin. This observation suggests a potential benefit of higher doses of nadroparin in the acute course after aSAH. We therefore hypothesise that treatment with high-dose nadroparin will improve clinical outcome in endovascularly treated patients with aSAH.

**Methods and analysis:**

This is a single-centre, prospective, phase II randomised controlled trial. From January 2022, all eligible patients will be recruited. 100 patients will be randomised to the intervention arm, that is, nadroparin two times per day 5700 AxaIU, or the control arm, that is, nadroparin once daily 2850 AxaIU in patients with body weight ≤100 kg or once daily 5700 AxaIU in patients with body weight >100 kg, both for up to 21 days. The trial includes a 6-month follow-up period. The primary objective is 30-day mortality rate. Secondary outcomes include assessment of DCI, complications during admission, discharge location, clinical outcome (modified Rankin Scale), quality of life and total healthcare costs at 3 and 6 months follow-up.

**Ethics and dissemination:**

Approval was obtained from the Medical Research Ethics Committee of the Amsterdam UMC, location Academic Medical Center (AMC) (MREC-number 2020_192), and recruitment has begun. The study results will be submitted for publication in peer-reviewed journals and presented at international conferences.

**Trial registration number:**

NCT04507178.

STRENGTHS AND LIMITATIONS OF THIS STUDYUse of randomised controlled design minimises selection bias and enhances internal validity.Stratified randomisation by World Federation of Neurosurgical Societies score ensures balance in clinical severity between groups.Single-centre design may limit generalisability to broader patient populations and healthcare settings.Blinded outcome assessment reduces risk of detection bias for follow-up measurements.Absence of interim analysis may delay detection of potential harm or benefit during trial progression.

## Introduction

 Aneurysmal subarachnoid haemorrhage (aSAH) is a severe type of stroke associated with high rates of morbidity and case fatality rate. Approximately 33% of patients do not survive within 3 months after the haemorrhage, and 20% remain significantly dependent on others for daily care and activities.^1^ Given that half of these patients are younger than 55 years old, the impact on productive life years is substantial, affecting both economic and social aspects.^2^

One of the major complications of aSAH is delayed cerebral ischaemia (DCI), which occurs in 20–40% of patients and can result in brain infarction, permanent brain damage and poor clinical outcomes.^2^,^4^ Cerebral vasospasm, in reaction to aneurysm wall rupture and subarachnoid blood, was long considered to be the principal determinant contributing to DCI. This concept has led to routine treatment with nimodipine, a calcium channel blocker, with only modest success on the prevention of DCI and clinical outcome.^5^ Growing experimental and clinical evidence has shown that not necessarily vasospasm, but the activation of several key pathophysiological pathways may be the principal determinant of DCI. Cortical spreading depressions, endothelial dysfunction, procoagulant activity causing microthrombosis, neuroinflammation, oxidative stress, necrosis and apoptosis may all contribute to brain injury after the acute intracranial circulatory arrest of the initial haemorrhage.^6^,^9^ Due to this partly understood complex pathophysiology, many different treatment strategies have been proposed, of which none seem sufficient for preventing or treating secondary brain damage.^6^

Several studies, including one conducted recently in 2021, have argued the possible beneficial effect of heparin in patients with aSAH.^10^,^19^ Recent studies highlight that heparin has extensive anti-inflammatory and immune-regulating properties, which are independent of its anticoagulant effects.^20 21^ Among others, heparin binds oxyhaemoglobin, blocks the activity of free oxygen radicals, antagonises endothelin-mediated vasoconstriction, binds to several cytokines and all chemokines (anti-inflammatory) and several growth factors (antimitogenic and antifibrotic).^20^,^23^ In addition, heparin antagonises the activation of pathways that seem responsible for ischaemic brain damage in patients with aSAH (figure 1). Henceforth, not DCI prevention in itself, but rather modulation of several pathophysiological processes could be targeted by heparin treatment.

**Figure 1 F1:**
[figure not shown]
Activation of pathways after aneurysmal rupture and possible heparin targets (adapted image from Budohoski *et al*).^6^ BBB, blood-brain barrier; CBF, cerebral blood flow; CBV, cerebral blood volume; EDHF, endothelium-derived hyperpolarizing factor; ET-1, endothelin-1; ICP, intracranial pressure; IL-6, interleukin-6; K+, potassium; NO, nitric oxide; NOS, nitric oxide synthase; Oxy-Hb, oxyhaemoglobin; PAF, platelet-activating factor; PGI2, prostacyclin; TNFR, tumour necrosis factor receptor; vWF, von Willebrand factor.

One observational study investigated the impact of postinterventional continuous intravenous unfractionated heparin (UFH) in patients with aSAH who underwent endovascular treatment. Findings indicated that the patients receiving therapeutic UFH experienced fewer instances of vasospasm and DCI during their hospital stay compared with those treated with prophylactic low-molecular weight heparin (LMWH).^24^ In contrast, there was no beneficial effect on outcome after 6 months of follow-up. However, as patients with therapeutic UFH were only treated for 7 days, and DCI continues to develop until 14 days after aneurysm rupture, this study could have underestimated the effect of heparin.

We retrospectively analysed patients with aSAH who were treated with high-dose LMWH (nadroparin 5700 AxaIU two times per day until discharge with a median duration of 17 days) and found a significant reduction of in-hospital mortality compared with patients treated with low-dose LMWH (nadroparin 2850 AxaIU once daily until discharge) (5% and 23%, respectively).^25^ In addition, discharge to home was significantly higher in patients who received high-dose LMWH, compared with low-dose LMWH (40% and 17%, respectively). In summary, some studies suggest that higher doses of heparin could improve the clinical outcomes for patients with aSAH, but high-level evidence is lacking. To address this gap, a randomised controlled trial (RCT) is necessary. This phase II trial aims to evaluate the efficacy and safety of high-dose nadroparin combined with standard care, providing essential evidence to determine whether to proceed to a larger phase III trial.

Nadroparin was selected as the investigational product over other LMWHs or UFH based on both practical and theoretical considerations. In our institution, therapeutic use of UFH requires intensive monitoring and titration, which can only be performed in the intensive care unit (ICU) setting. This would necessitate prolonged ICU admission—up to 3 weeks—for all study participants, making it logistically and ethically unfeasible. Furthermore, achieving stable anticoagulant levels with UFH is notoriously difficult in critically ill patients, with the activated partial thromboplastin time often failing to accurately reflect heparin activity, thus increasing the risk of both underdosing and overdosing.^26 27^ Nadroparin, by contrast, has a more predictable pharmacokinetic profile, can be administered subcutaneously and allows for reliable monitoring via anti-Xa levels. Additionally, the potential non-anticoagulant, pleiotropic effects of heparins—such as modulation of neuroinflammation and apoptosis—are expected to be shared across both UFH and LMWHs.^22^ Thus, nadroparin was chosen as the most suitable agent to evaluate the therapeutic potential of heparins in this vulnerable patient population. We hypothesise that treatment with high-dose nadroparin significantly reduces 30-day mortality compared with standard care. To determine this potential benefit, we will conduct an RCT titled ‘Improving outcome in SubaraChnoid HEMorrhage wIth nAdroparin’ (ISCHEMIA). The ISCHEMIA trial challenges existing treatment paradigms, which are mostly aimed at blood-induced vasospasm and will be the first RCT to investigate the effect of high-dose LMWH in patients with aSAH.

## Methods and analysis

### Study design and setting

This trial is a single-centre phase II prospective randomised trial designed to evaluate the efficacy and safety of high-dose nadroparin combined with standard care in patients with aSAH following endovascular coiling. Eligible patients are randomly assigned to the intervention or control group after written informed consent is obtained. The trial pathway is illustrated in figure 2. The trial protocol has been registered in the National Institutes of Health ClinicalTrials database (number NCT04507178). The trial started randomisation in January 2022 and aims to include 100 patients within 4 years.

**Figure 2 F2:**
[figure not shown]
Flowchart. *Once daily 2850 AxaIU in patients with body weight ≤100 kg or once daily 5700 AxaIU in patients with body weight >100 kg. aSAH, aneurysmal subarachnoid haemorrhage; EQ-5D, EuroQol 5-Dimensions questionnaire; ISCHEMIA, Improving outcome in SubaraChnoid HEMorrhage wIth nAdroparin; IU, international units; mRS, modified Rankin Scale; TICS-M, Modified Telephone Interview for Cognitive Status.

### Participants

The study population consists of patients with aSAH admitted to the Amsterdam UMC location University of Amsterdam. Patient selection is based on the following inclusion and exclusion criteria.

#### Inclusion criteria

Spontaneous aSAH confirmed by CT or lumbar puncture with the causative aneurysm confirmed by CT-angiography and/or digital subtraction angiography.Coiling of the causative aneurysm within 72 hours of initial SAH.Informed consent before the first scheduled administration of the study medicine.Adult age (≥18 years).

#### Exclusion criteria

Stent-assisted coiling.Use of anticoagulant or dual antiplatelet medication postcoiling for other indications.Incomplete aneurysm occlusion/partial coiling.Intraparenchymal haemorrhage.Arteriovenous malformation.Pregnancy.Contraindications for LMWH:History of heparin-induced thrombocytopenia.(Suspicion of) active arterial or venous bleeding.History of haemorrhagic diathesis due to coagulation disorders (with the exception of disseminated intravascular coagulation)Severe hypertension: uncontrolled hypertension with a persistent mean arterial pressure (MAP) >135 mm Hg.History of hypertensive or diabetic retinopathy.History of active infectious endocarditis.Severe renal impairment (creatinine clearance <30 mL/min).Patient or substitute decision-maker (SDM) lacks proficiency in Dutch and English.Proven and active COVID-19 infection.

### Recruitment and consent

If patients are eligible for the study, they, or their legally appropriate SDM, will be informed about the study’s rationale, possible risks and study burden. A sample consent form is provided in online supplemental appendix C. To optimally modify several key pathophysiological intravascular factors, it is paramount that the study medication is started as early as possible, at least within 24–72 hours after coiling. Therefore, there will be a maximum reflection period until the first scheduled administration of the study medication (mostly within 24 hours after the coiling procedure, unless other reasons necessitate postponement; see section ‘Interventions’). Subjects, or their legally appropriate SDM, who have given consent for inclusion in the study can decide to exit the study at any time for any reason without any consequences.

### Allocation and randomisation

After obtaining informed consent, patients will undergo randomisation with stratification for World Federation of Neurosurgical Societies (WFNS) score. Five strata were defined, one for each WFNS score. Within each stratum, separate randomisations are performed between the intervention and control group to ensure a balanced randomisation based on disease severity. This is particularly important because, in patients with high-grade WFNS scores, goals of care may shift toward comfort-focused measures, which can independently affect mortality outcomes regardless of the intervention. Stratification by WFNS grade helps mitigate this potential source of bias. Randomisation is conducted using a web-based permuted block system and performed by the principal investigator or executive researcher. This system employs permuted blocks of variable sizes, ranging from two to six patients, to minimise the predictability of group allocation and ensure balanced sample sizes in each study arm. Patients are randomised in a 1:1 ratio and assigned to one of the two treatment arms.

### Interventions

Patients in the intervention group will receive a high dose of LMWH, specifically nadroparin 5700 AxaIU administered two times per day. Treatment will start as soon as the redeemed safe is available, but no later than 24–72 hours after coiling and will continue for 21 days following the initial SAH. For safety reasons, high-dose nadroparin will only be administered to patients with a secured aneurysm. The current inclusion criteria consider both the time of ictus and the timing of coiling. Only patients who undergo coiling within 72 hours of ictus are eligible for inclusion, with most starting nadroparin within 24 hours after coiling. In clinical practice, the majority of eligible patients present on the day of ictus or the following day and are coiled within 24 hours. Since DCI typically develops between days 4 and 10 after SAH, this time frame is considered an appropriate therapeutic window. If discharged home before 21 days, the treatment will stop on discharge. If hospitalisation extends beyond 21 days, the prophylactic dose will be continued until discharge or until the patient is mobilised for more than 6 hours per day. The high dose of nadroparin used in this study is solely considered therapeutic in patients weighing under 70 kg. This fixed dosing approach reflects the study’s focus not solely on anticoagulant effects but also on the broader pleiotropic properties of LMWH, such as anti-inflammatory and endothelial-stabilising actions. In general, target anti-Xa levels for nadroparin are unknown. Based on observed anti-Xa levels in subjects with a therapeutic weight-based dose, reference ranges are regularly around 0.6–1.2 IU/mL. However, it remains uncertain whether benefits and harms of nadroparin are optimally maintained in this range.^28^

In the control group, patients will receive standard care with a prophylactic dose of LMWH (nadroparin; 2850 AxaIU once daily for those weighing ≤100 kg, or 5700 AxaIU once daily for those weighing >100 kg), starting within 24 hours after coiling and continuing until discharge or when mobilised for at least 6 hours daily.

Patients with anticoagulants receive reversal agents on admission as standard care. In the case of vitamin K antagonists and heparin derivatives, patients in the intervention group will only start with high-dose LMWH after receiving reversal agents, with an international normalised ratio ≤1.5, and 24 hours after the initial bleeding (unless a craniotomy is indicated). In the case of direct oral anticoagulants (DOACs) use, high-dose LMWH will not be administered until 48 hours after receiving the last dose of DOAC since there are often limited options to reverse its action. Antiplatelets are often not counteracted unless a craniotomy is performed. In the case of antiplatelet use, high-dose LMWH will be postponed until 24 hours after the initial bleeding. In the case of dual antiplatelet therapy, a cardiologist will be consulted to assess whether it’s possible to switch to high-dose LMWH. If this is not possible, the patient will be excluded. The investigator or treating physician can decide to withdraw a subject from the study for urgent medical reasons. If it is revealed after inclusion that one of the exclusion criteria was present in a certain patient on admission, this patient will remain included in the study and this is recorded as a protocol violation. Depending on the criterion, actions are undertaken. For instance, nadroparin can be stopped (history of heparin-induced thrombocytopenia, history of hypertensive or diabetic retinopathy, endocarditis) or switched to an alternative type of LMWH or the higher dose will be switched for a prophylactic dose (severe renal impairment, intestinal tract bleeding). If nadroparin is not available or not tolerated, mostly due to skin reactions, other LMWHs can be administered depending on local availability and according to the doses listed in online supplemental appendix A. In case of mild renal failure (creatinine ≥30 mL/min and <50 mL/min), the dose of LMWH in the intervention arm will be reduced by 25%. Emergency surgical procedures (eg, lumbar puncture, insertion of ventricular catheter or lumbar drain) and procedures for bleeding in patients receiving a higher dose of LMWH conform to standard routine clinical care. A flowchart is included in online supplemental appendix B.

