### Data safety analysis

Adverse events (AEs) and serious AEs (SAEs) will be recorded in our electronic case report form (CRF). Only AEs occurring during hospital admission that are unrelated to the SAH must be reported to the institutional review board and principal investigator. All SAEs will be reported without undue delay after obtaining knowledge of the events. In this trial, certain SAEs are anticipated in patients with SAH, including severe hyponatraemia (serum sodium <125 mmol/L), hypokalaemia (serum potassium <3.5 mmol/L), fever, hydrocephalus, DCI, periprocedural aneurysm rupture, rebleed, delirium, Terson’s syndrome, epilepsy, diffuse parenchymal swelling, nosocomial meningitis, pneumonia and urinary tract infection. These expected SAEs will be recorded in the CRF and do not require further reporting.

A data and safety monitoring board (DSMB) is installed for this trial including a neurologist, neurosurgeon and independent statistician. The members are not involved in the trial and have no competing interests. Their tasks, responsibilities and working procedures are outlined in a charter. The DSMB will review safety data and the incidence of (S)AEs at three specified intervals: After 30, 60 and 100 patients have completed their 30-day follow-up. The DSMB will conduct ongoing safety surveillance, particularly regarding the occurrence of SAEs related to an increased risk of haemorrhagic complications. Additionally, the DSMB will advise on the continuation of the trial and may recommend the Steering Committee of the ISCHEMIA trial to terminate the trial if there is clear and substantial evidence of harm. No interim analysis is planned in this trial.

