There are several strengths to this trial. Patients will receive high-dose nadroparin only during their hospital admission and for a maximum of 21 days, ensuring no postdischarge burden. Additionally, nadroparin is relatively inexpensive, suggesting that future implementation would face minimal financial constraints. The study includes both primary and secondary objectives, with secondary outcomes covering a wide range of clinical parameters, offering a comprehensive assessment of the potential benefits and risks of high-dose nadroparin. Rigorous methodology, including stratified randomisation and intention-to-treat analysis, enhances the reliability and validity of the results. By selecting 30-day mortality as the primary outcome, the study employs a clear, objective and clinically significant endpoint, reducing subjective interpretation and providing a definitive assessment of the treatment’s impact.

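### Interventions and Discussion give different end-of-treatment rules for high-dose patients discharged before day 21 to a non-hospital facility

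*Protocol article*

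**What the plan says.** In the Protocol article, Interventions, high-dose treatment "will continue for 21 days following the initial SAH". Two qualifications follow. The first concerns early discharge: "If discharged home before 21 days, the treatment will stop on discharge". The second concerns long stays: "If hospitalisation extends beyond 21 days, the prophylactic dose will be continued until discharge", or until the patient is mobilised. Nothing is said about discharge before day 21 to a place other than home. For the control arm the same section has the prophylactic dose "continuing until discharge or when mobilised for at least 6 hours daily", with no destination attached.

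The Discussion, listing strengths, says: "Patients will receive high-dose nadroparin only during their hospital admission and for a maximum of 21 days, ensuring no postdischarge burden". The Abstract gives only a duration, "both for up to 21 days", and no discharge rule.

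Three other places depend on the rule:

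- Sample size calculation names compliance with study medication as one of the feasibility results.
- Statistical analysis removes non-adherent patients from the per-protocol and as-treated analyses.
- Data safety analysis says "Only AEs occurring during hospital admission that are unrelated to the SAH must be reported" to the review board and the principal investigator. It also says that adverse events (AEs) and serious adverse events (SAEs) are recorded in the case report form, and that SAEs are reported without that admission limit.

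**The concern.** The two sections part company for one type of patient: an intervention patient discharged before day 21 to rehabilitation, a nursing facility or a similar place. Under Interventions the 21-day default still holds, because the only early stop is discharge home. Under the Discussion the high dose ends with the admission.

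Three things follow.

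1. **Adherence.** A patient whose high dose stops at transfer to a nursing facility is compliant under the Discussion and non-compliant under Interventions. A patient who continues there is classified the other way round. Who leaves the per-protocol and as-treated sets would then turn on discharge destination, which reflects recovery and is linked to a secondary outcome of the trial (discharge to home).
2. **The contrast between arms.** Under Interventions, a transferred intervention patient stays on the high dose while a transferred control patient has stopped. Under the Discussion, both have stopped.
3. **Bleeding counts.** Under Interventions the high dose can outlast the admission. The Abstract describes complications as those during admission, and mandatory AE reporting is tied to the same period. The Outcomes section defines non-major bleeding as whatever is reported and not major, so the count depends on reporting. Control treatment ends at discharge at the latest, so on-treatment bleeds missed after discharge would all belong to the intervention arm. That would understate harm in a trial meant to assess safety.

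**Working it through.** **Inputs** (retrospective high-dose group unless stated)

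- In-hospital mortality 5%, against 23% on low dose (Introduction; Sample size calculation).
- Discharge to home 40%, against 17% on low dose (Introduction).
- Treatment: "nadroparin 5700 AxaIU two times per day until discharge with a median duration of 17 days" (Introduction).
- Planned arm size 50 (Sample size calculation).

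**The plan's own figure.** 23% − 5% = 18 percentage points, as stated. The odds ratio from the rounded rates is (0.05/0.95)/(0.23/0.77) = 0.176. Rates that round to 5% and 23% give 0.153 to 0.200, so the stated 0.19 is compatible. These inputs are sound enough to use.

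**The rules side by side, intervention arm, discharge before day 21**

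| Destination | Interventions | Discussion |
|---|---|---|
| Home | stop | stop |
| Another hospital | continue to day 21 (default) | continue, if the admission is taken to include the second hospital |
| Rehabilitation or nursing facility, not a hospital | continue to day 21 (default) | stop |

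Only the last row is a clear conflict.

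**Discharged alive to somewhere other than home, at any time**

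- High dose: 100% − 40% − 5% = 55% (54% to 56% allowing for rounding); of 50 patients, 27.5.
- Low dose: 100% − 17% − 23% = 60%.
- If the home percentage is of survivors only (an assumption), the high-dose figure is 0.60 × 95% = 57%, so little changes.

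**Discharged elsewhere before day 21.** The documents do not give this share, so it can only be bounded.

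- Lower bound: a median of 17 days means half had finished treatment by then. If every home discharge and every death fell in that half, 50% − 40% − 5% = 5% remain; of 50 patients, 2.5.
- Upper bound: all such discharges came before day 21, giving 55%; of 50 patients, 27.5.
- Range: about 3 to 28 of 50.

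The lower bound counts treatment days, while the trial's 21 days run from the bleed. It needs 17 treatment days to end before day 21, so treatment must start within 21 − 17 = 4 days of the bleed. Interventions says that most eligible patients present on the day of the bleed or the next day, are coiled within 24 hours, and mostly start within 24 hours of coiling. That fits, but it is not shown for the retrospective group.

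**Length of the disputed exposure.** For a patient at the median, at most 21 − 17 = 4 days, less the delay from bleed to first dose. It is longer for those who leave sooner.

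**The case against.** The best case on the other side has four parts.

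*The conflict is inferred from silence.* Interventions never says that dosing goes on in a nursing facility, and the Discussion sentence lists a strength rather than setting a rule. This has some force, but the 21-day default is explicit and discharge home is its only stated exception at discharge. The same section uses discharge without a destination for the control arm and for long stays, and the article treats discharge to home as a separate outcome. It is therefore hard to read the word home as loose drafting.

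*Safety follow-up is in place.* A reader might infer that it is undefined for these patients. The documents do not support that. AEs and SAEs go into the case report form, SAEs are reported without an admission limit, and the data and safety monitoring board reviews data after 30-day follow-up, which is past day 21. The admission limit applies to what must be reported to the review board and principal investigator. What remains is possible under-capture of non-serious bleeds after discharge.

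*The size is unknown.* A reader might take the 55% to mean that most intervention patients are affected, or halve it to about 27% by assuming that timing is unrelated to destination. Neither is supported: the 55% covers discharge at any time, and no passage supports independence. Transfers to another hospital can also satisfy both sections. This objection stands in full.

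*The primary analysis does not move, and detail may sit in the full protocol or analysis plan.* The first part is right: intention to treat keeps every patient. A detailed adherence definition may indeed be elsewhere. The point here is that two statements in this article disagree, which is different from a detail being left out.

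**Conclusion.** The point holds in a limited form. For discharge before day 21 to a non-hospital facility, the article gives two different ends of high-dose treatment. Planned exposure is ambiguous rather than undefined, because each section gives an answer. What depends on the choice is the reference for compliance, membership of the per-protocol and as-treated sets, and, if treatment may continue after discharge, the completeness of non-serious bleeding counts in the intervention arm only. The intention-to-treat comparison of 30-day mortality is untouched.

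The number affected cannot be fixed from the documents. Early discharge to anywhere other than home lies between about 5% and 55% of the arm. The non-hospital part is unknown and could be small. These figures assume that the trial arm resembles the retrospective high-dose group and, for the lower bound, that treatment there began within about four days of the bleed. The correction is worth making because it is cheap and removes a contradiction in a treatment rule. No view is taken on which rule is right.

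**What to change.** 1. Reconcile Interventions and Discussion into one end-of-treatment statement that covers every discharge destination, including transfer to another hospital. The choice of rule is the sponsor's.
2. Judge compliance, and exclusion from the per-protocol and as-treated sets, against that single statement.
3. Count major and non-major bleeding in both arms to the same fixed day after the bleed, late enough to cover all high-dose treatment wherever it is given. Day 30, when the primary outcome is assessed, would be convenient.

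The first two items cost only wording. The third means asking about bleeding after discharge or transfer. Randomisation began in January 2022, so for patients already enrolled the information may have to come from records and may be less complete.
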